#### Placebo

The placebo consists of 4 capsules per day (2 each morning and night), containing an inert substance (starch filler, silica coating, with taste and colouring added) matched for the colour, taste, and smell of SLT.

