### Randomisation and allocation concealment

A university staff member, external to the research team, conducted computerised random sequence allocation using a unique random number generator in Microsoft Excel. A permuted block randomisation strategy was used with an allocation ratio of 1:1. Allocation was concealed using batch numbers generated with the unique random number generator by the same staff member; these were sent directly to the manufacturer. After eligibility is confirmed, participants are allocated to the next numbered box of product by a member of the research team. This is a double-blind trial, so both participants and the research team are blinded to allocation. Furthermore, all data analyses will be conducted blinded to treatment allocation.

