### Statistical analyses and data management

The study will largely employ a mixed-model design with a between-subjects factor of group (treatment vs. placebo) and within-subjects factor of time (baseline vs. endpoint). Analyses of variance (ANOVAs) will be conducted to assess differences in continuous outcome measures between the two groups. All tests will be one tailed, α = 0.05. As there are only two testing points for the primary outcome measures (baseline and endpoint), data from any participants failing to complete follow-up will not be included in the final analysis.

All data will be stored on a secure server with two back-up copies on external hard drives. Paper-based forms will be digitised and the original copies stored in locked filing cabinets in secure rooms that require swipe card access at Western Sydney University Campbelltown campus. All participants are de-identified upon randomisation and referred to on all forms with a participant ID. A password-protected spreadsheet stored on the secure server links participant names to ID codes to all for re-identification to occur if required. As this is a relatively small investigator-initiated pilot trial, a data monitoring committee and auditing process are not required.

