### Compliance, success of blinding, safety, and adverse events

After baseline measurements, the first 6 weeks of medication will be dispensed. The second 6 weeks of medication will be dispensed at the midpoint of the study. An additional week of medication (7 weeks total) will be provided at both baseline and midpoint in case there is an unforeseen delay in attending the follow-up appointments. Participants will be required to return any unused medication at midpoint and endpoint; this will be used to determine compliance. The number of returned capsules will be counted by a university staff member external to the research team to further reduce the potential of unblinding. The blood samples collected at baseline, midpoint, and endpoint will also be used in a separate pharmacokinetics study to assess the plasma concentrations of bioactive components of SLT. Eight SLT markers will be assessed: ginsenosides Rg1, Re, Rb1, and Rc and ginkgolides A, B, C, and bilobalide.

At the study midpoint and endpoint, participants will be asked to which treatment condition they think that they have been allocated. Responses of SLT, placebo, or unknown will be recorded. Responses will be checked against the condition allocated at the end of the trial to assess success of blinding. An exit interview will be conducted upon study completion to ascertain further information about participants’ experiences during the trial, e.g. information on health-related expectations, factors influencing compliance/adherence, and any impacts that the trial medication might have had on quality of life. Participants who exit the study early will be contacted via telephone and requested to complete the exit interview.

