To monitor safety, participants will be referred to a local commercial laboratory (Laverty) at screening and endpoint. Standard blood safety tests (full blood count and liver and renal function tests) will be carried out. If participants receive an abnormal blood safety test result at baseline, they will not be enrolled in the study, and they will be encouraged to follow up their results with their regular health professional. Adverse events will be closely monitored throughout the course of the study. In the case of a serious adverse event, if the study drug is suspected as a potential cause and identifying treatment allocation is essential to the participant receiving appropriate medical care, unblinding of that participant only will occur. This will be done by the university staff member external to the research team who generated the computerised random sequence allocation.

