## Discussion

SLT has shown efficacy in improving cognition in people with vascular dementia and in enhancing neuronal activity and cerebral perfusion in healthy adults and in seniors with vascular dementia, respectively. Given that preclinical and pilot clinical trials have also shown SLT to be safe and well tolerated, and because it addresses multiple mechanisms implicated in the pathology of MCI, it should be evaluated in this cohort.

This study has some limitations. First, although an a priori sample size calculation has been determined, the study still has a relatively low power (80%) to detect an effect. Having said this, the project is a pilot study — the first of its kind in an MCI cohort — and the outcomes will inform the design of a high-powered conversion study to test whether SLT can prevent or delay the development of dementia. Second, participant burden is quite high during the physiological assessment battery due to the number of measures and the length of the tasks. However, this is necessary given the trial’s secondary aim to assess the mechanisms of action of SLT in people with MCI. Scheduled breaks have been put in place to minimise participant fatigue.

MCI is a heterogeneous syndrome with complex pathophysiologies. Current efforts to address the cognitive deficits in MCI using single-target pharmaceuticals, such as cholinesterase inhibitors, have yielded poor and inconsistent results, highlighting the need for new and innovative strategies. This randomised controlled trial focuses on SLT, a potential treatment that has been shown to address MCI’s multi-faceted pathophysiology in preclinical studies and has yielded positive results from pilot clinical trials in healthy adults and people with vascular dementia. The outcomes of this trial will inform the development of future interventional research involving people with MCI, such as a large-scale conversion study.

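### The one stated rule for breaking an individual code requires suspicion of the study drug as well as clinical need; the suspicion condition protects nothing and can be deleted

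*Protocol article*

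**What the plan says.** The rule stands in the safety paragraph of the protocol article, under Compliance, success of blinding, safety, and adverse events. It applies to a serious adverse event and operates "if the study drug is suspected as a potential cause and identifying treatment allocation is essential to the participant receiving appropriate medical care". When it is met, "unblinding of that participant only will occur". The code is opened by the staff member outside the research team who generated the allocation sequence.

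No other part of the article gives a route to an individual code break:

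- Randomisation and allocation concealment sets up the blind: "This is a double-blind trial, so both participants and the research team are blinded to allocation".
- Statistical analyses and data management provides for re-identification, but of names and not of treatment: "A password-protected spreadsheet stored on the secure server links participant names to ID codes". The same section says that "a data monitoring committee and auditing process are not required", so no committee is described that might hold the allocation.
- The blinding questionnaire uses the allocation only once the study is over: "Responses will be checked against the condition allocated at the end of the trial to assess success of blinding".

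**The concern.** Two different questions can be asked after a serious adverse event. One is whether the capsules may have caused it. The other is whether the treating team needs to know what the participant was taking in order to treat it. The first matters for reporting and for the safety profile of the product. The second is the reason to open a code in an emergency.

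The rule requires a yes to both. A participant whose event is not attributed to the drug, but whose care depends on the allocation, meets the need and fails the rule. What is at stake is the care of that participant. A staff member holding the code and working from the article's wording would find no instruction covering the request.

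**Working it through.** No figure in the plan is involved, so the check is one of logic.

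**Inputs**, all from the safety paragraph:

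- A: the event is a serious adverse event.
- B: the study drug is suspected as a possible cause.
- C: the allocation is essential to appropriate care.

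**Rule as stated:** unblind if A and B and C.

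**Rule without the causality condition:** unblind if A and C.

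Within serious adverse events (A true), B and C give 2 × 2 = 4 combinations:

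| Drug suspected (B) | Allocation essential (C) | Stated rule | Rule without B |
|---|---|---|---|
| yes | yes | unblind | unblind |
| yes | no | not covered | not covered |
| no | yes | not covered | unblind |
| no | no | not covered | not covered |

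The stated rule covers 1 of the 4 and the shortened rule covers 2. No combination covered now is lost. The only row that differs is the third: not suspected, allocation essential. These are counts of rule conditions. They say nothing about how many participants would fall in each row.

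**Does condition B restrain needless unblinding?** It does not. Where C is false, neither version opens the code, whatever B is. Where C is true, opening the code is by definition needed for care. All the restraint comes from C.

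**Is the third row a real possibility?** The protocol's own pharmacology makes it plausible. Table 1, under SLT formulation background, lists an anti-platelet aggregation effect for ginkgo. Rationale for the current project counts inhibition of platelet aggregation among the actions of SLT. Participants are 60 or older, and the criteria listed under Inclusion/exclusion criteria do not name anticoagulant or antiplatelet use. Suppose a participant trips, breaks a hip and needs urgent surgery. Nobody need suspect the capsules of causing the fall, yet the surgical team may need to know whether the participant is on a product with antiplatelet action. This is an illustration. The article gives no frequency for such events and none is assumed here.

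**The case against.** The strongest reply is that the sentence gives a sufficient condition and not an exclusive one. It says when unblinding will happen. It does not say that unblinding will happen in no other circumstances, and the word *only* limits which participant is unblinded, not when. That stands. A reader might infer that the protocol bars a code break for an unattributed event, or that it would deny a participant needed care. The text does not support either inference. What remains is that the one rule it does state carries a needless condition.

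A second reply is that a journal article condenses a longer protocol, which may hold a fuller emergency procedure. This weakens the point without removing it. The objection is to a condition that the article states, not to detail that it leaves out. Whether the full protocol has a further route cannot be known from the article.

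A third reply is that the excluded case is nearly empty. Being a potential cause is a low bar, and in a bleeding event the antiplatelet property would itself raise suspicion and satisfy the rule. The placebo is described as "containing an inert substance", so clinicians can often manage the participant as if on SLT without opening the code. The Discussion adds that "preclinical and pilot clinical trials have also shown SLT to be safe and well tolerated". All of this stands as a reason to expect very few cases. It also means that in the surgical example allocation might prove useful rather than essential. It does not give the causality condition a purpose, because the test of need would screen out the merely useful cases without it.

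A reader might also want the rule widened to medical emergencies that are not serious adverse events, or a step added to record causality before the code is opened. Neither follows from the defect shown. Events that are not serious fall outside the rule because of its first condition, not because of the causality condition.

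**Conclusion.** The point holds as a minor matter of patient safety. The only individual unblinding rule in the article makes suspicion of the drug a precondition alongside clinical need. That precondition does nothing except leave outside the rule a serious event that is not attributed to the drug and for which allocation is essential to care.

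Its practical size cannot be derived from the document and should be very small. There is no effect on error rates, power or the interpretation of the results. The conclusion rests on two readings: that the conditions are cumulative, which the wording makes plain, and that no other individual route is stated, which is true of the article but cannot be checked against the full protocol. The change is a cheap improvement, not a correction on which the trial depends.

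**What to change.** Delete the ten words between *if* and *identifying* in the unblinding sentence. The rule would then say that, after a serious adverse event, a participant is unblinded, and that participant alone, whenever knowing the allocation is essential to his or her appropriate medical care. The type of event, the restriction to one participant and the person who opens the code stay as they are.

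The cost is one edited sentence. Trial status reports recruitment as ongoing, and Study design, ethics, and setting already provides for telling the investigators, the registry and the ethics committee of protocol changes. The downside is possibly a very small number of extra single-participant code breaks, limited by the test of need that remains.

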## Discussion

SLT has shown efficacy in improving cognition in people with vascular dementia and in enhancing neuronal activity and cerebral perfusion in healthy adults and in seniors with vascular dementia, respectively. Given that preclinical and pilot clinical trials have also shown SLT to be safe and well tolerated, and because it addresses multiple mechanisms implicated in the pathology of MCI, it should be evaluated in this cohort.

This study has some limitations. First, although an a priori sample size calculation has been determined, the study still has a relatively low power (80%) to detect an effect. Having said this, the project is a pilot study — the first of its kind in an MCI cohort — and the outcomes will inform the design of a high-powered conversion study to test whether SLT can prevent or delay the development of dementia. Second, participant burden is quite high during the physiological assessment battery due to the number of measures and the length of the tasks. However, this is necessary given the trial’s secondary aim to assess the mechanisms of action of SLT in people with MCI. Scheduled breaks have been put in place to minimise participant fatigue.

MCI is a heterogeneous syndrome with complex pathophysiologies. Current efforts to address the cognitive deficits in MCI using single-target pharmaceuticals, such as cholinesterase inhibitors, have yielded poor and inconsistent results, highlighting the need for new and innovative strategies. This randomised controlled trial focuses on SLT, a potential treatment that has been shown to address MCI’s multi-faceted pathophysiology in preclinical studies and has yielded positive results from pilot clinical trials in healthy adults and people with vascular dementia. The outcomes of this trial will inform the development of future interventional research involving people with MCI, such as a large-scale conversion study.

### Trial status

The trial began recruitment on 3 April 2017 and is currently ongoing.

## Abbreviations

ACh: Acetylcholine
ADAS-Cog: Alzheimer’s Disease Assessment Scale-Cognitive subscale
ATP: Adenosine triphosphate
BNT: Boston Naming Test
BVRT: Benton Visual Retention Test
COWAT: Controlled Oral Word Association Test
DASS-21: 21-item Depression, Anxiety, Stress Scale
D-KEFS: Delis-Kaplan Executive Function System
DNA: Deoxyribonucleic acid
DSM-IV: Diagnostic and Statistical Manual of Mental Disorders, 4th Edition
ECG: Electrocardiogram
EEG: Electroencephalography
FBC: Full blood count
FDA: Federal Drug Administration
GDS: Geriatric Depression Scale
GP: General practitioner
IQCODE: Informant Questionnaire on Cognitive Decline in the Elderly
LFT: Liver function test
MCI: Mild cognitive impairment
MoCA: Montreal Cognitive Assessment
NIA-AA: National Institute on Aging-Alzheimer’s Association
Pfeffer FAQ: Pfeffer Functional Activities Questionnaire
QOL-AD: Quality of Life in Alzheimer’s Disease (scale)
RAVLT: Rey Auditory Verbal Learning Test
RCFT: Rey Complex Figure Test
RFT: Renal function test
SLT: Sailuotong
SOD: Superoxide dismutase
TICS-M: Telephone Interview for Cognitive Status-Modified
ToPF: Test of Premorbid Functioning
WMS-IV: Wechsler Memory Scale, 4th Edition
WNK: Wei Nao Kang
